### Sample Size Estimation

As shown in Figure 3, the sample size for the RCT was calculated using G*Power software (Heinrich-Heine-Universität Düsseldorf), selecting the *F* tests for analysis of variance: repeated measures, within-between interaction. The calculation was based on a precision level of 0.05, a study power of 95%, an effect size of 0.20, and a correlation coefficient of 0.5 among the outcome measures. Therefore, the minimum required sample size for each group is 56. A low effect size of 0.20 was chosen based on previous interventions addressing SQ [33]. After adjusting for a 10% dropout rate, the sample size was increased to 60 medical students per group. Given that this is a 2-arm RCT, a total of 120 medical students will be required to complete the study.

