### Randomization and Allocation Concealment

As participants will be recruited from 2 different universities, a stratified randomization method will be used to ensure balance between the groups from each university. Eligible students will be grouped by university and gender before random selection. Gender will serve as a matching factor during the stratified randomization process to ensure a comparable number of female and male students are recruited from both universities.

Data will be collected from volunteer medical students, and the researchers will have no influence on the randomization process or access to future allocations. Each participant will be assigned an identification number and listed before being randomized into either the ISHE or ICBT-I group using online randomization software [34]. A total of 60 students will be allocated to each group.

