### Data Analysis

Data will be analyzed using SPSS version 29 (IBM Corp.). Descriptive statistics will be used to obtain information on dropout rates, recruitment, and completeness. All participants will be included in the intention-to-treat analysis for assessing the main efficacy of the intervention, with no planned interim analysis for efficacy or futility. The baseline characteristics of participants will be presented according to their randomized group, with no inferential statistical tests performed at this stage.

For the RCT design, outcome measures will be assessed for normality and presented as either means with SD or medians with IQR, depending on the data distribution. Participants’ characteristics will be summarized using descriptive statistics, with categorical data presented as frequencies and percentages, and continuous data presented as means (SD) or medians (IQR). Normality will be tested using the Kolmogorov-Smirnov and Shapiro-Wilk tests.

Changes in all outcome measures (ie, SOL, TST, NOA, WASO, SQ, SE, dysfunctional beliefs about sleep, presleep arousal, and SHI) from pretreatment (T0) to the first (T1), second (T2), and third (T3) time points will be assessed for treatment effects using repeated measures analysis of variance. Both treatment and time interaction effects will be examined. Paired samples *t* tests will then be conducted within each condition to evaluate possible simple or main effects. Significant findings and statistical trends will be further analyzed using Cohen *d* effect size, which accounts for the correlation between pre- and posttreatment values.

Potential confounding factors, particularly class year and gender, will be addressed and analyzed as variables that may influence the research outcomes. These factors will be incorporated into the analysis through both univariate and multivariate linear regression analyses, allowing for the isolation of each factor and its association with the outcomes of interest.

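### Randomisation is stratified by university and gender, but the treatment test as described includes neither; the cost is a mildly conservative test and a small loss of power

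*Protocol article*

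**What the plan says.** Randomization and Allocation Concealment makes two factors part of the design. On university: "a stratified randomization method will be used to ensure balance between the groups from each university". On both: "Eligible students will be grouped by university and gender before random selection". On gender: "Gender will serve as a matching factor during the stratified randomization process". Class year is not mentioned there.

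Data Analysis states that changes in the outcomes "will be assessed for treatment effects using repeated measures analysis of variance", and then: "Both treatment and time interaction effects will be examined". No stratum or covariate is named for that model. Sample Size Estimation powers the trial on the same family of test: "analysis of variance: repeated measures, within-between interaction".

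A later paragraph of Data Analysis deals with gender and class year: "Potential confounding factors, particularly class year and gender, will be addressed and analyzed as variables that may influence the research outcomes". It continues: "These factors will be incorporated into the analysis through both univariate and multivariate linear regression analyses, allowing for the isolation of each factor", the stated aim being each factor's association with the outcomes. The paragraph mentions no treatment term. University appears nowhere in Data Analysis.

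**The concern.** A factor used to balance the allocation belongs in the model that tests treatment. Stratifying removes that factor's contribution to the chance difference between arms. A model without the factor still counts its contribution as residual noise. The standard error is then too large, the test rejects too rarely under the null, and some power is lost.

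The article does say what will be done with gender, and it puts it in the wrong place. Gender and class year are fixed before randomisation, so they can differ between arms only by chance, and gender is meant to be balanced by design. They are prognostic factors, not confounders of the treatment comparison. A regression of outcome on each factor answers a prognostic question. It leaves the ICBT-I versus ISHE comparison unadjusted.

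**Working it through.** **Passages side by side**

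| Factor | In the randomisation | In the treatment ANOVA | In the separate regressions |
|---|---|---|---|
| University | Yes | Not named | Not named |
| Gender | Yes | Not named | Yes |
| Class year | No | Not named | Yes |

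The plan gives no figure on this point, so there is none to reproduce. The size has to be worked out under assumptions.

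**Inputs from the article:** 120 students, 1:1 allocation, alpha 0.05, correlation 0.5 between repeated measures, treatment-by-time as the powered test.

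**Assumptions, not in the article:** 65% female (78 women and 42 men), allocation exactly balanced within gender, true effect 0.5 SD, and gender explaining a share R² of the variance of the quantity tested, with R² between 0 and 20%.

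**Formula for the unadjusted test.** With balance within gender, the treatment difference has variance proportional to (1 − R²), but the unadjusted model estimates it as if proportional to 1. The actual type I error is therefore 2 × [1 − Φ(1.96/√(1 − R²))]:

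- R² = 2%: 0.048
- R² = 5%: 0.044
- R² = 10%: 1.96/√0.90 = 2.066, giving 0.039
- R² = 20%: 1.96/√0.80 = 2.191, giving 0.028

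**Which R² applies.** In a treatment-by-time test the comparison is of change within students. A gender effect that is constant over time is subtracted out, so R² is gender's share of the variance of *change*. For the between-group main effect or a single visit, a constant gender effect does not cancel, and R² is its share of the variance of the student mean or of that visit.

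**Simulation, without and with gender in the model.** The rows for change use two time points, where the test of change equals the treatment-by-time test. Each has 20,000 replicates, so the Monte Carlo standard error of a 5% rate is √(0.05 × 0.95/20,000) = 0.0015.

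| Quantity tested | Gender effect | Type I error, without / with | Power, without / with |
|---|---|---|---|
| Change | Constant over time, 10% | 0.050 / 0.050 | 0.775 / 0.775 |
| Change | 2% of change variance | 0.048 / 0.051 | 0.780 / 0.787 |
| Change | 5% of change variance | 0.043 / 0.050 | 0.780 / 0.797 |
| Change | 10% of change variance | 0.040 / 0.052 | 0.786 / 0.817 |
| Single visit | 10% | 0.041 / 0.054 | 0.786 / 0.814 |
| Single visit | 20% | 0.026 / 0.046 | 0.797 / 0.861 |

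On change, the power lost runs from 0 to about 3 points (0.817 − 0.786 = 0.031). On a single visit with R² = 20% it is about 6 points (0.861 − 0.797 = 0.064). University was not simulated. The formula covers it if R² is read as the joint share of both strata.

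**The case against.** Five points can be made for the plan.

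- **The effect on the powered test is close to nothing.** This stands, and it sets the size of the point. A constant gender effect cancels, and what remains is conservative. It cannot manufacture a finding in favour of ICBT-I.
- **An article leaves covariates to the analysis plan.** This stands for details such as how visits enter a secondary regression. Silence on university alone would not be a finding. But the article does state how gender and class year enter, and that choice keeps a design factor out of the treatment test.
- **The gender wording is partly about recruitment.** The article gives the purpose of gender matching as comparable numbers of women and men from both universities. If the software did not in fact balance arms within gender, the unadjusted test would hold its nominal level. Adjustment would still gain precision.
- **Class year is not a stratum.** This is correct. The conservative-test argument does not apply to it, and it enters only as a prognostic covariate.
- **Secondary prognostic regressions are legitimate.** They are, provided they are labelled as such.

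Two stronger readings are tempting. A reader might infer that the ANOVA and the two kinds of regression give rival treatment estimates, from which one could be picked after the results are seen. The text does not support this: it describes associations of each factor with the outcomes and states no treatment term. A reader might also infer that the regressions pool visits as if independent and so inflate false positives. The article says nothing about pooling, and such an error would concern the test of gender or class year, not of treatment.

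**Conclusion.** The mismatch is real: two factors shape the allocation, and the described treatment model contains neither. The separate regressions do not repair this, because as written they yield no adjusted treatment difference, and calling these factors confounders misstates their role in a randomised comparison.

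The consequence is modest. For treatment-by-time, type I error is about 0.040 to 0.050 and about 0 to 3 points of power are lost, if gender explains up to 10% of change variance. Only for the between-group main effect or a single-visit comparison does the loss grow, to about 6 points at an R² of 20%. These figures rest on the assumed R², gender split and effect of 0.5 SD, and on allocation balanced within gender. Nothing here suggests bias towards either arm. The change is worth making because it costs almost nothing.

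**What to change.** In Data Analysis, name one model that estimates the ICBT-I minus ISHE difference, and put university and gender in it as fixed between-subject factors. Where treatment-by-time is tested, include their interactions with time as well, because main effects alone leave that test unchanged. Add class year as a prespecified prognostic covariate on the same footing. Call all three stratification or prognostic factors, not confounders. Keep the univariate and multivariate regressions only as descriptive analyses of how each factor relates to the outcomes. Settle this before the analysis begins.

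The cost is a few sentences and baseline data that are easily available. University takes 1 degree of freedom, gender 1 and class year 2 (years 1 to 3), so 4 of the 120 − 2 = 118 between-subject residual degrees of freedom. With the four time points that Data Analysis names (T0 to T3), the time interactions take 4 × 3 = 12 of 118 × 3 = 354 within-subject residual degrees of freedom.

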### Research Aim and Hypotheses

This study aims to elucidate the effects of improved SQ on executive function. The following hypotheses will be investigated in the trial:

ICBT-I will lead to a significant improvement in SQ compared with the SHE intervention at 1 month (T2), 3 months (T3), and 6 months (T4) postintervention.ICBT-I will lead to a significant improvement in executive functioning compared with the SHE intervention at 1 month (T2), 3 months (T3), and 6 months (T4) postintervention.ICBT-I will lead to a significant improvement in total sleep time (TST), SOL, number of awakenings (NOA), wake time after sleep onset (WASO), and sleep efficiency (SE) compared with the SHE intervention at 1 month (T2), 3 months (T3), and 6 months (T4) postintervention.Dysfunctional beliefs, attitudes about sleep, presleep worry, and sleep hygiene will significantly mediate the between-group differences in study outcomes at 1 month (T2), 3 months (T3), and 6 months (T4) postintervention.

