Regarding the fourth hypothesis, mediation analyses will be conducted to explore whether changes in the outcome measures from pretreatment to posttreatment are significantly mediated by dysfunctional beliefs and attitudes about sleep, sleep hygiene, and presleep worry. The analysis will follow the traditional mediation model, where the direct, indirect, and total effects are defined in terms of the linear regression coefficients [51]. For example, when the mediation effect size is medium (ie, SM) and the intraclass correlation coefficient is 0.2, with 4 repeated measures, the Sobel method would require 191 participants to achieve 80% power. By contrast, the product-of-coefficients and bootstrap methods would require 188 and 185 participants, respectively, to achieve the same power [52]. This study will adopt the bootstrap method for mediation analysis due to its flexibility in terms of sample size requirements.

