Given the negative psychological and physiological consequences of poor SQ, such as burnout, suicidal ideation, and reduced empathy toward patients, this trial provides an opportunity to explore a nonpharmacological intervention for improving SQ and executive function among medical students. The findings will help bridge the important research gap identified in previous studies on CBT-I across diverse populations. These studies rarely focus on specific groups such as health professionals or young adults (eg, medical students). If poor SQ causally alters executive function, it is plausible to hypothesize that (1) CBT-I will improve both SQ and executive functioning and (2) the pathway through improved SQ will facilitate the treatment effects on executive functioning [54]. Furthermore, this trial provides a unique opportunity to expand existing knowledge, as only a few RCTs have investigated the roles of hyperarousal mediators (eg, presleep worry), cognitive mediators (eg, dysfunctional beliefs and attitudes about sleep), and behavioral mediators (eg, sleep hygiene) in CBT-I [20].

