### Strengths and Limitations

This study will be the first RCT in Malaysia to investigate SQ and executive function using a dTMT among medical students. Additionally, it is the first to examine potential mediators, such as presleep worry and sleep hygiene, in the relationship between beliefs about sleep and SQ in this population. A representative sample will be recruited through a simple random sampling technique, allowing the findings to be extrapolated to public medical students in Malaysia and potentially other countries with similar educational demographics.

Nevertheless, this study has important limitations. The sample will be drawn only from medical students at UPM and UKM, meaning it may not be representative of all government-based undergraduate medical students in Malaysia. Additionally, the risk of response biases cannot be ruled out, particularly regarding subjective sleep experiences, which may influence the findings. Participants may also be inclined to provide socially desirable answers. Studies on Asian cultures have shown that, due to the cultural emphasis on modesty, Asians are likely to suppress the expression of positive emotions, which could impact the accuracy of self-reported data [55]. This study will use only a quantitative research approach, which may limit a comprehensive understanding of medical students’ perspectives and views on poor SQ symptoms and the strategies they use to address the issue. Additionally, there is a risk that participants may provide socially desirable answers when responding to the research instruments.

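### The mediation analysis does not match hypothesis 4 in contrast or time points, and the article conflicts on what the exposure is

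*Protocol article*

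**What the plan says.** The protocol article describes mediation in four places.

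- **Research Aim and Hypotheses, hypothesis 4.** There are three candidate mediators: beliefs and attitudes, worry before sleep, and hygiene. The hypothesis is that they "will significantly mediate the between-group differences in study outcomes at 1 month (T2), 3 months (T3), and 6 months (T4) postintervention". The effect to be explained is the randomised contrast, at three follow-up times.
- **Data Analysis.** "Regarding the fourth hypothesis, mediation analyses will be conducted", and their stated aim is to "explore whether changes in the outcome measures from pretreatment to posttreatment are significantly mediated by dysfunctional beliefs and attitudes about sleep"; the other two candidate mediators are listed there as well. The model is given as follows: "The analysis will follow the traditional mediation model, where the direct, indirect, and total effects are defined in terms of the linear regression coefficients". Inference is by bootstrap. No exposure variable is named, and neither arm nor T2, T3 or T4 appears in this paragraph.
- **Expected Findings and Implications.** Beliefs and hygiene are listed among "cognitive mediators (eg, dysfunctional beliefs and attitudes about sleep), and behavioral mediators (eg, sleep hygiene) in CBT-I", which agrees with hypothesis 4.
- **Strengths and Limitations.** The trial is described as examining "potential mediators, such as presleep worry and sleep hygiene, in the relationship between beliefs about sleep and SQ in this population". Here beliefs are the starting variable.

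**The concern.** An indirect effect is defined only once the exposure is fixed. Mediation of the arm difference, mediation of change over time and mediation of a beliefs-to-sleep association are three questions with three null hypotheses. Only the first involves the treatment contrast.

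This matters here because the comparator is active. Table 1 gives both arms psychoeducation on sleep hygiene and progressive muscle relaxation, and the section on internet-based SHE acknowledges overlapping content. Similar improvement in both arms is plausible, above all for hygiene and presleep worry. It is less so for beliefs, because ISHE has no cognitive restructuring. If both arms improve alike, a model that leaves arm out can still give a bootstrap interval excluding zero, and that result could be taken as evidence of how CBT-I works.

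**Working it through.** **Passages side by side**

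| Section | Effect to be mediated | Exposure | Role of beliefs | Times |
|---|---|---|---|---|
| Hypothesis 4 | between-group difference | arm (implied) | mediator | T2, T3, T4 |
| Data Analysis | pre-to-post change | not named | mediator | pretreatment to posttreatment |
| Expected Findings | effects of CBT-I | treatment (implied) | mediator | none given |
| Strengths and Limitations | beliefs-SQ relation | beliefs | exposure | none given |

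Hypothesis 4 and its own analysis differ in contrast and in time points. The last row conflicts with the other three on the role of beliefs.

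**Plan's own figures.** The only numbers given for mediation are sample sizes of 191, 188 and 185 for three methods. They cannot be rebuilt because the path coefficients are not stated, and they do not settle the exposure.

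**Does the choice of exposure matter when the arms are identical?** This was checked by simulation.

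*From the article:* planned N = 120 (Sample Size Estimation); enrolled N = 48 + 49 = 97 (Results); bootstrap inference; two-sided 5%.

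*Assumed:* both arms improve the mediator by d = 0.3 to 0.8 SD; mediator-outcome slope r = 0.3 or 0.5; pre-post correlation 0.5; for the beliefs model, both paths equal to r. The arm effect is zero on mediator and outcome throughout.

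*Indirect effect a × b under each reading:*

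- Pooled pre-post: a = mean mediator change, b = slope of outcome change on mediator change, adjusted for the sum of the two mediator scores. True value −d × r; for d = 0.5 and r = 0.3 this is −0.5 × 0.3 = −0.15, although the arms are identical.
- Beliefs as exposure: a = mediator on beliefs, b = outcome on mediator given beliefs. True value r × r; 0.3 × 0.3 = 0.09 and 0.2 × 0.2 = 0.04.
- Arm as exposure: a = mediator on arm, b = outcome on mediator given arm. True value 0 × r = 0.

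Share of simulated trials whose 95% percentile bootstrap interval excludes zero (500 resamples; 1,000 trials per setting, or 2,000 for beliefs at N = 120):

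| Model | N = 97 | N = 120 |
|---|---|---|
| Pooled pre-post | 71–100% | 82–100% |
| Beliefs as exposure, paths 0.3 | 67% | 82% |
| Beliefs as exposure, paths 0.4 | 95% | 99% |
| Beliefs as exposure, paths 0.5 | not run | >99% |
| Arm as exposure, same data as row 1 | 3.7–6.0% | 4.4–6.5% |
| Arm as exposure, same data as rows 2–4 | 5.0–7.2% | 5.0–6.5% |

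The simulation standard error at 5% with 1,000 trials is √(0.05 × 0.95 / 1,000) ≈ 0.7 percentage points. A smaller run at N = 120 (200 to 500 trials, 200 to 400 resamples) agreed and added weaker paths: with beliefs paths of 0.2, beliefs as exposure was significant in 33% and arm as exposure in 1.4%.

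The arm models here used change or post scores without baseline covariates. Adding baseline covariates leaves the true a-path at zero when the arms are identical.

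**The case against.** The best defence is that the Data Analysis paragraph is expressly tied to hypothesis 4, which is about between-group differences. A traditional mediation model needs an exposure, and in a two-arm trial the obvious one is arm. Earlier in the same section, changes from pretreatment are assessed for treatment effects, so change may simply name the dependent variable. The beliefs-as-exposure sentence is a loosely worded novelty claim in the Discussion, and no Methods passage plans that model. The paragraph also speaks of exploring, and hypothesis 4 is not the primary comparison. Covariate choice is often left to an analysis plan.

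Much of this stands. A reader might infer that the planned analysis cannot test hypothesis 4. The text does not support that: with arm as exposure and change as outcome, the described model does test mediation of a between-group difference, though only from pre to post. A reader might also take the 67 to 100% figures as the plan's false-positive rate. They are not. They are the power of two other models to detect associations that the simulation assumed, and the Methods specify neither model.

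The defence does not remove the mismatch. The stated target of the analysis differs from the hypothesis it is assigned to, in contrast and in time. The pooled reading is also not far-fetched: the sample size illustration cites an intraclass correlation with 4 repeated measures, and the preceding analysis plans paired tests within each condition.

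**Conclusion.** The point holds as a conflict in the text. Hypothesis 4 concerns between-group differences at T2, T3 and T4; its analysis concerns pretreatment-to-posttreatment change with the exposure unnamed; and one Discussion sentence gives beliefs a different role from the other three passages.

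The size depends on the reading adopted. With arm as exposure, rejection under identical arms is about 4 to 7% (1.4% at paths of 0.2), so nothing material is lost beyond the missing T2 to T4 time points. With a pooled pre-post model or beliefs as exposure, a significant result needs no arm difference: about 67 to 100% under the assumed moderate paths, and 33% for beliefs paths of 0.2. The percentages rest on assumed improvements and path sizes. That a model without arm can be significant when the arms are identical does not.

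This should be corrected before analysis. It affects a stated hypothesis, not the primary comparison.

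**What to change.** In Data Analysis:

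- Name randomised arm (ICBT-I versus ISHE) as the exposure.
- Model the mediator on arm, adjusted for the baseline mediator.
- Model the outcome on the mediator, adjusted for arm, baseline outcome and baseline mediator.
- Take the mediator at a time before the outcome it is meant to explain, for the T2, T3 and T4 outcomes named in hypothesis 4. T1 precedes all three.
- Base any hypothesis 4 claim only on the bootstrap confidence interval for the arm indirect effect a × b.

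In Strengths and Limitations, align the sentence with hypothesis 4 and Data Analysis, or label the beliefs-to-SQ path as exploratory and observational.

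The cost is wording: the data and the bootstrap are unchanged, and the baseline values are already collected. The drawback is that an arm-based indirect effect is harder to show as significant. Randomisation protects the arm-to-mediator path but not the mediator-to-outcome path, so even the corrected analysis needs cautious causal wording. T1 and T2 data are reported as complete for the enrolled participants, so the model should be fixed and dated before anyone analyses them.
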